### Screening

We screen patients who sign up for a mass cataract surgery event in a regional hospital in Cianjur, West Java, Indonesia. Patients will be asked for information regarding personal identification, history of systemic and ocular diseases, and allergies. They then will undergo ophthalmology examination including uncorrected visual acuity (UCVA) and best corrected visual acuity (BCVA), intraocular pressure using non-contact tonometry (NCT), biomicroscopy slit lamp, and indirect fundoscopy to evaluate anterior and posterior chambers. Lens opacity will then be measured using LOCS III criteria. We will also examine ECD, coefficient of variety (COV), and hexagonality of endothelial cell layers using a specular microscope (REM 4000, Rodenstock, Germany), central corneal thickness (CCT) using Anterior Segment Optical Coherence Tomography (ASOCT), and biometry. Blood samples will be then drawn from patients to measure serum AA, MDA, and TAC.

### Randomization, blinding and allocation concealment

The subjects will be allocated into three groups: Group 1 will receive oral vitamin C 500 mg, three times daily pre- and postoperatively, Group 2 will receive it only preoperatively, and Group 3 will receive a placebo. Participants will be randomly assigned to the study groups using a computer-generated block randomization sequence with a block size of four. The randomization sequence will be prepared by an independent researcher who will not be involved in patient recruitment or outcome assessment. Allocation concealment will be ensured using sequentially numbered, sealed, opaque envelopes. The study will be conducted in a double-blinded manner. Operating surgeons, examiners, laboratory analysts, and study participants will be blinded to group allocation throughout the study period. Participants will be followed up for seven weeks, and data will be analyzed after the minimum required number of participants has been reached.
Figure 1 shows the planned CONSORT flow diagram of participants screening, randomization, follow-up, and analysis.

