### Sample size calculation

A total sampling method was used. The sample size was determined based on the primary outcome of postoperative corneal endothelial cell density (ECD) loss, referring to a previous study by Chee et al.
^
14
^ The minimal sample size calculated for this study was 36 subjects for each group (95% confidence interval, power 80%, β = 0.20, α = 0.05, SD = 201 ​​cell/mm
^2^, expected difference = 132 ​​cell/mm
^2^, subjects should have at least 132 ​​cell/mm
^2^ difference of ECD loss after phacoemulsification in the intervention group). With a 10% additional for anticipating loss to follow-up subjects, the minimal sample size needed was 40 for each group.

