### Intervention

Patients will be divided into three groups, each with 40 samples. The first group (n=40) will receive 500 mg oral vitamin C three times daily (1500 mg/day) for one week before surgery to four weeks after surgery. The second group (n=40) will receive 500 mg oral vitamin C three times daily (1500 mg/day) for one week before surgery and a placebo after surgery. The last group (n=40) will receive a placebo one week before surgery to four weeks after surgery. Oral vitamin C 1500 mg/day was chosen based on pharmacokinetic evidence showing that this dosage can achieve stable plasma concentrations and approach a steady-state level during short-term administration.
^
15
^

To minimize potential bias related to surgical variability, all phacoemulsification procedures will be performed using standardized surgical techniques. The surgeries will be conducted by experienced cataract surgeons using the same phacoemulsification machine and standardized operative settings. Key intraoperative parameters, including ultrasound power, irrigation parameters, and the type of ophthalmic viscosurgical device (OVD), will be standardized across all procedures.

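### A block size of four does not fit three equal groups, so the stated randomisation does not guarantee the planned 40 per group

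*Protocol article*

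**What the plan says.** The Randomization section describes the allocation in two statements. First, "The subjects will be allocated into three groups": vitamin C before and after surgery, vitamin C before surgery only, and placebo. Second, "Participants will be randomly assigned to the study groups using a computer-generated block randomization sequence with a block size of four".

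The planned group sizes stand elsewhere. The Sample size section reports "The minimal sample size calculated for this study was 36 subjects for each group" and then "With a 10% additional for anticipating loss to follow-up subjects, the minimal sample size needed was 40 for each group". The Intervention section says "Patients will be divided into three groups, each with 40 samples" and repeats n=40 for each arm. No ratio is given in words, but three groups of 40 mean 1:1:1 and 120 patients in total.

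The Laboratory analysis section mentions computer-generated randomisation to three groups again, without a ratio or block size. The Study status section says that the study was in data processing when the article was submitted.

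**The concern.** With permuted blocks and equal allocation, each complete block must hold the same number from every arm, so with three arms the block size must be a multiple of three. Four is not. Either the block size is misreported, or the list was built in blocks that are unequal within themselves, by a rule the article does not give.

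The article chose to state a block size, and the stated value does not fit its own number of arms and arm sizes. It is therefore not a detail left to a fuller document. At stake are the reproducibility of the randomisation, which a reader cannot reconstruct from the text, and the per-arm numbers on which the power statement rests.

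**Working it through.** **Inputs from the protocol article.** Three groups and block size 4 (Randomization); 40 per group, 120 in total (Intervention); 36 per group before loss, 10% loss, "power 80%, β = 0.20, α = 0.05, SD = 201" cells/mm² and "expected difference = 132" cells/mm² (Sample size calculation). Two-sided testing is assumed, as the article does not state sidedness.

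**1. The plan's own figure.** n per group = 2 × [(1.960 + 0.842) × 201 / 132]² = 36.4. The article states 36; rounding up would give 37. For loss, 36 / 0.90 = 40, and 36 × 1.10 = 39.6, which also rounds to 40. The sample size reproduces to within one patient and does not depend on the block size.

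**2. Divisibility.** 4 = 3 × 1 + 1. A block of four that contains every arm is 2:1:1, with one extra slot. 120 / 4 = 30 blocks, so there are 30 extra slots, and each arm has 30 patients plus the extra slots that fall to it.

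**3. Extra slot assigned at random (an assumption; the article gives no rule).** Arm sizes are 30 + multinomial(30; 1/3, 1/3, 1/3).
- SD of one arm's size: √(30 × 1/3 × 2/3) = 2.58, around a mean of 40.
- P(exactly 40/40/40) = 30! / (10!³ × 3³⁰) = 0.027.
- Summing over all splits: P(smallest arm below 36) = 0.106; expected smallest arm 37.4; expected gap between largest and smallest arm 5.3.

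**4. Effect on power.** Standardised difference = 132 / 201 = 0.657; two-sided t-test at 0.05; 10% loss in each arm.
- Exact balance, 36 v 36: 78.5%. The normal approximation gives 79.6%, consistent with the planned 80%.
- Random extra slot, averaged over all splits and all three pairs of arms: 78.3%.
- Random extra slot, the two smallest arms only, averaged over all splits: 76.9%.

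**5. Structures that give exactly 40/40/40.** Blocks of 3 (120 / 3 = 40 blocks), 6 (20 blocks) or 12 (10 blocks). Blocks of four also do so if each arm receives the extra slot in exactly 10 of the 30 blocks.

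**The case against.** The strongest reply is that blocks of four and groups of 40 can be reconciled. 120 is divisible by 4, and an extra slot rotated evenly gives 40 each. A block size of four might also mean four per arm, that is, blocks of 12. Both readings are arithmetically sound, so the article does not show that 40 per group is out of reach. But neither reading is in the text, and each needs the sentence completed or corrected.

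The second reply is that imbalance of this kind does little harm. That stands. Step 4 shows an average loss of about 0.2 percentage points. Random differences in arm size do not bias the comparison, and the article provides for an independent sequence generator, sealed opaque envelopes and blinding.

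A reader might infer something stronger: that one arm was doubled in every block, giving 60/30/30, with power of 66% after 10% loss, or 48% at a Bonferroni level of 0.05/3. The documents do not support this. The Intervention section gives n=40 for every arm, which speaks against a 2:1:1 design. Even under that split, the 66% applies only to the two small arms (27 v 27); comparisons with the doubled arm (54 v 27) keep 78.6%. The 48% must be read against 63% for the planned 36 v 36 at the same Bonferroni level, so over half of the fall from 80% comes from the multiplicity adjustment, not the block size.

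**Conclusion.** The point holds as an error in the stated randomisation rule. A block size of four does not fit three equal groups, and without a rule for the fourth slot the scheme neither guarantees 40 per group nor can be reproduced. It does not show that the trial is underpowered, biased or in fact unbalanced.

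The probabilities of about 2.7% for exact balance and about 11% for an arm below 36 rest on three assumptions: 120 patients, 30 complete blocks, and a fourth slot assigned at random. The power comparison also assumes 10% loss in every arm and the article's own SD and difference. Under another rule the arm sizes would differ, and only the list itself can settle which rule was used.

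**What to change.** The study is in data processing, so advice to randomise in other blocks comes too late. The list exists and should be checked.

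- **If the blocks were a multiple of three (3, 6 or 12):** correct the block size in the Randomization section and state the 1:1:1 ratio there.
- **If blocks of four were really used:** state in the Randomization section how the fourth slot was assigned and the actual allocation ratio. In the Sample size and Intervention sections, give the numbers actually randomised in place of 40 per group, and restate the power on those numbers.

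The cost is one look at the randomisation list. The first case then needs a one-line correction. The second needs a few sentences and a short power recalculation.

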**Figure 1. f1:**
[figure not shown]
Planned CONSORT flow diagram of participants screening, randomization, follow-up, and analysis.

### Intervention

Patients will be divided into three groups, each with 40 samples. The first group (n=40) will receive 500 mg oral vitamin C three times daily (1500 mg/day) for one week before surgery to four weeks after surgery. The second group (n=40) will receive 500 mg oral vitamin C three times daily (1500 mg/day) for one week before surgery and a placebo after surgery. The last group (n=40) will receive a placebo one week before surgery to four weeks after surgery. Oral vitamin C 1500 mg/day was chosen based on pharmacokinetic evidence showing that this dosage can achieve stable plasma concentrations and approach a steady-state level during short-term administration.
^
15
^

To minimize potential bias related to surgical variability, all phacoemulsification procedures will be performed using standardized surgical techniques. The surgeries will be conducted by experienced cataract surgeons using the same phacoemulsification machine and standardized operative settings. Key intraoperative parameters, including ultrasound power, irrigation parameters, and the type of ophthalmic viscosurgical device (OVD), will be standardized across all procedures.

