### Statistical analysis

Data from this study will be recorded and analyzed by IBM SPSS 20.0. Sample personal identification, including demographic and clinical characteristics, will be reported in a descriptive analysis. Data distribution of numerical variables will be assessed using the Shapiro–Wilk test with normal distribution will be presented as mean (standard deviation [SD]); non-normal distribution will be reported as median (interquartile range [IQR]). Nominal data will be reported in frequency and percentage. We will use Pearson’s chi-squared test for categorical data. For comparisons among the three groups, one-way ANOVA will be used for normally distributed data, while the Kruskal–Wallis test will be used for non-normally distributed data. Significant group differences will be followed by post-hoc pairwise comparisons using Bonferroni correction for ANOVA or Dunn’s test following the Kruskal–Wallis analysis to account for multiple testing. Pearson’s test will be used to test the correlation between data in aqueous humor and serum. A p-value of less than 0.05 (p < 0.05) will be considered statistically significant.

Effective phacoemulsification time (EPT) and total surgical duration will be included as covariates in the statistical analysis to account for their potential influence on postoperative endothelial outcomes. Multivariable analysis will also be conducted to control for potential confounding variables, including smoking status, occupational exposure, ultraviolet (UV) light exposure, and dietary intake of vitamin C. These variables will be collected through structured questionnaires during the screening.

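### More than one surgeon operates, but surgeon is named in neither the allocation nor the analysis, which costs precision in the primary ECD comparison

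*Protocol article*

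**What the plan says.** On who operates, the Intervention section of the protocol article states: "The surgeries will be conducted by experienced cataract surgeons using the same phacoemulsification machine and standardized operative settings". The section on randomization, blinding and allocation concealment also uses the plural: "Operating surgeons, examiners, laboratory analysts, and study participants will be blinded to group allocation throughout the study period". Neither gives the number of surgeons or their caseloads.

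On surgical variability, the Intervention section says: "To minimize potential bias related to surgical variability, all phacoemulsification procedures will be performed using standardized surgical techniques". It adds: "Key intraoperative parameters, including ultrasound power, irrigation parameters, and the type of ophthalmic viscosurgical device (OVD), will be standardized across all procedures".

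On allocation, participants are to be "randomly assigned to the study groups using a computer-generated block randomization sequence with a block size of four". No stratification factor is named.

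On analysis, the three arms are compared by one-way ANOVA or, for non-normal data, Kruskal-Wallis. The Statistical analysis section then says: "Effective phacoemulsification time (EPT) and total surgical duration will be included as covariates in the statistical analysis". A multivariable analysis is to handle potential confounders, "including smoking status, occupational exposure, ultraviolet (UV) light exposure, and dietary intake of vitamin C". Surgeon is not in either list. The section does not say whether the unadjusted test or the adjusted model is the primary comparison.

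**The concern.** The primary outcome is loss of endothelial cells during and after an operation, so the person operating is a plausible source of variation in it. The protocol treats surgical variability as a threat and chooses two surgical covariates to deal with it, but not the operator.

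Those two covariates are an incomplete substitute. The Introduction says that hard nuclei need longer phacoemulsification, and eligibility spans LOCS III grades 4 to 6, so EPT and duration mix case difficulty with operator. They may miss differences in technique that do not change the time taken. They are also recorded at surgery, one week after treatment has started. Surgeon identity should not depend on treatment, because the surgeons are blinded.

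If the unadjusted ANOVA or Kruskal-Wallis test is the primary comparison, even this partial control is absent. What is at stake is the width of the confidence interval for the ECD difference, and so power, in a trial whose sample size has almost no margin.

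**Working it through.** **Inputs from the Sample size calculation section:** SD 201 cells/mm2, difference 132 cells/mm2, α = 0.05, power 80%, 36 per group, 40 after a 10% allowance for loss. Sidedness is not stated.

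**Assumed, not in the documents:** the share ρ of the ECD-loss variance that lies between surgeons, taken as 0.05 to 0.20. For two surgeons with equal caseloads whose means differ by d, the between-surgeon variance is d²/4, so d = 2 × 201 × √ρ. The range then corresponds to d = 402 × 0.224 ≈ 90 up to 402 × 0.447 ≈ 180 cells/mm2.

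**1. The plan's own figure.** n = 2 × [201 × (1.960 + 0.842)/132]² = 36.4 per group, two-sided, against the stated 36. A one-sided test would give 29, which does not match. With 10% loss, 36/0.9 = 40. The stated figures reproduce, and leaving surgeon out does not make them wrong.

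**2. Power with a surgeon term, if the SD of 201 already contains surgeon variation.** Residual SD = 201 × √(1 − ρ). Power = Φ(132/(SD × √(2/36)) − 1.960).

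| ρ | SD | 132/SE | Power |
|---|---|---|---|
| no surgeon term | 201.0 | 2.786 | 79.6% |
| 0.05 | 195.9 | 2.859 | 81.6% |
| 0.10 | 190.7 | 2.937 | 83.6% |
| 0.20 | 179.8 | 3.115 | 87.6% |

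In sample-size terms the gain is 1/(1 − ρ): 1/0.95 = 1.05 to 1/0.80 = 1.25, or 5% to 25% more participants.

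**3. If the SD of 201 does not contain surgeon variation.** Total SD = 201/√(1 − ρ). Without a surgeon term, power at 36 per group is 77.5%, 75.3% and 70.3% at ρ = 0.05, 0.10 and 0.20. The documents do not say which case applies.

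**4. Simulation check** (two arms of 36, three surgeons with equal caseloads, 4,000 runs per setting).

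| ρ | Type I error, no surgeon term | Power without | Power with |
|---|---|---|---|
| 0.10 | 4.6% | 79% | 81% |
| 0.20 | 5.6% | 81% | 85% |

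Simulation error on the type I figures is about 0.35 percentage points, so both are near 5%. The simulated gains are smaller than those in step 2. The formula ignores the degrees of freedom spent and the cost of uneven surgeon mix. Also, with only three surgeons drawn at random, the realised between-surgeon variance is on average below its nominal share.

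**5. Chance imbalance is not a second harm.** Take two surgeons with equal caseloads and 40 per arm. The unadjusted SE is 201 × √(2/40) = 44.9, a variance of 2020. The SD of the difference in surgeon mix is √(2 × 0.25/40) = 0.112. At d = 100 this shifts the arm difference by 11.2 cells/mm2 (variance 125); at d = 200, by 22.4 (variance 500). Removing it gives √(2020 − 125) = 43.5 and √(2020 − 500) = 39.0. These equal the SEs with surgeon in the model, 194.7 × √(2/40) = 43.5 and 174.4 × √(2/40) = 39.0. The shift from imbalance and the wider SE are the same quantity.

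**The case against.** The strongest reply has three parts.

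- **Nothing is stated wrongly.** This is a condensed article, its confounder list is open-ended, and a surgeon term could stand in a fuller document. That is right as far as it goes: silence does not show that surgeon is excluded. But the article does choose its surgical covariates, EPT and duration, and the operator is not one of them. A better-founded covariate is available at little cost.
- **Surgical variability is already addressed.** Experienced surgeons, standardised technique, one machine, fixed settings and OVD type, and adjustment for EPT and duration should all shrink or absorb part of any operator effect. This stands, and it makes the formula gains above an upper estimate for a model that already holds those two covariates.
- **The size is assumed.** This also stands. The plural shows only that there is more than one surgeon; two would fit.

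A reader might infer that an excess of one surgeon's cases in an arm could bias the trial or pass for a vitamin C effect more often than the nominal 5%. The documents do not support that. Patients are individually randomised and the surgeons are blinded. Chance imbalance is already counted in the unadjusted SE, and the simulated type I error stays near 5%.

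A reader might also want each surgeon's cases spread across the randomisation sequence. Under permuted blocks this tends to worsen balance. In a simulation of 120 patients, three arms and two surgeons (block sizes 3, 6 and 12), consecutive runs of 60/60 gave an imbalance SD of 0 and runs of 50/70 gave 2 to 3 percentage points. Alternating surgeons gave 12 to 13. The Study status section also puts the trial in data processing, so operating lists and stratification can no longer change.

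**Conclusion.** The point holds as an avoidable loss of precision. More than one surgeon operates, surgeon is named in neither the allocation nor the covariates, and the stated group test has no covariates. EPT and duration cover the operator only in part. There is no bias and no inflation of type I error.

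If surgeon explains 5% to 20% of the variance within the SD of 201, a surgeon term takes power at 36 per group from about 80% to between 82% and 88% by formula. The simulated gains were about 2 points at a 10% share and 4 points at 20%. The gain is smaller again if EPT and duration are already in the model. These figures rest on an assumed variance share and on the unadjusted α of 0.05 used in the sample size section. The direction is clear; the size cannot be settled from the documents.

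**What to change.** Before unblinded analysis:

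- Take the operating surgeon for each case from the operative record.
- State that the primary ECD comparison is the model with arm and surgeon as factors, pooling surgeons with very few cases. One-way ANOVA and Kruskal-Wallis as described cannot carry this term.
- Report the number of cases by surgeon and arm.

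The timing matters because a surgeon term added after the allocation is known would look chosen on the results. If unblinding has already happened, which the documents do not say, present the surgeon-adjusted result as a labelled sensitivity analysis.

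The cost is one factor in the model and a few degrees of freedom, more if there are many surgeons. It also requires that the operative records identify the surgeon, which the article does not say.

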### Post-intervention evaluation

Patients will be asked to come a week after screening. Firstly, they asked the side effects of the supplementation, including gastrointestinal disorders (nausea, diarrhea, epigastric pain). Second blood samples will be then drawn to measure post-intervention serum AA, MDA, and TAC.

Sampling for oxidative stress in the aqueous humour will be performed twice, pre- and post-phacoemulsification. During surgery, after the initial incision, 0.2 mL of aqueous humor will be taken using a 1 cc syringe with a 30 G cannula. Phacoemulsification will then be conducted using standard operating procedure to intraocular lens implantation. Another 0.2 mL of aqueous humor will then be taken three minutes after removing the viscoelastic as a post-phacoemulsification sample. This sampling volume is within the range commonly used in aqueous humor biomarker studies and is considered safe under surgical conditions. Because the sampling will be performed through the surgical incision and the anterior chamber will subsequently be maintained with a balanced salt solution, anterior chamber stability will not be affected.
^
16,
17
^ The pre-phacoemulsification aqueous humour samples will be analysed for ascorbic acid (AA), total antioxidant capacity (TAC), and malondialdehyde (MDA), while the post-phacoemulsification samples will be analysed for MDA levels only. Intraoperative parameters, including effective phacoemulsification time (EPT) and total surgical duration, will be recorded for each procedure. All patients will receive topical medications: levofloxacin 5 mg/mL every three hours for one week, prednisolone acetate 10 mg/mL every three hours for 1 week, and tapered down in 4-6 weeks.

Every patient will be evaluated one day, one week, four weeks, and six weeks post-phacoemulsification to measure study parameters and signs of complications, i.e. inflammation or infection. Patients who experience side effects or complications, including toxic anterior segment syndrome (TASS) or endophthalmitis during the duration of follow-up will be exempted from the study and managed according to the standard operational procedure of the Department of Ophthalmology, Faculty of Medicine, University of Indonesia.

